## Introduction

Delirium is a common postoperative complication, particularly in patients above the age of 65 years, and its causes are still largely unexplored [1]. Nevertheless, the effects of delirium are very serious for patients and, in some cases, can even drastically affect quality of life and even life expectancy. The incidence of postoperative delirium (POD) in older patients is 5% to 10% on average but can be higher in high-risk procedures such as total joint arthroplasty [2]. POD is therefore a frequent and life-threatening complication. At the center of this clinical picture is a functional disorder of the brain. Patients are affected symptomatically by disorientation, restlessness, hallucinations, or anxiety [3]. Despite these impressive and often serious symptoms, POD is often recognized late, and successful intervention is delayed [4]. However, it should be noted that the more time elapses before the diagnosis is made, the higher the probability of a severe and complicated course of POD. POD is associated with prolonged hospital stays, extended ventilation times, increased care requirements, and higher mortality rates [5]. Recovery from POD has considerable intraindividual variability, ranging from hours to months, and can present as a hypoactive, hyperactive, or mixed subtype, characterized by symptoms such as apathy, confusion, agitation, delusions, and signs of sympathetic arousal [6]. The pathophysiology of POD is not yet fully understood, but it is hypothesized to be related to acute disruptions in neurotransmitter levels and neuroinflammation [1]. Risk factors for POD include preoperative impaired cognitive and general health status, frailty, medical comorbidities such as hypotension and hypoxia, and exposure to psychoactive drugs [7]. Postoperative neuroinflammation, which is a major contributor to the development and progression of POD, can be exacerbated by complications such as infections, pulmonary issues, and hypoxemia [8]. The use of certain anesthetics has also been linked to long-term alterations in brain morphology and function, particularly at the extremes of age [9,10]. It is known from previous studies that the plasma levels of neuron-specific enolase and S-100 β protein may correlate with POD [11]. However, there are currently no valid laboratory tests for diagnosis. Furthermore, apart from an avoidance strategy for possible triggering drugs, there are only a few effective preventive and therapeutic approaches [3,12,13]. Existing models rely on clinical variables or single biomarkers. Our study integrates multiomics with advanced machine learning (ML) to explore novel predictive signatures and underlying biological mechanisms.

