### Sample Size Considerations

The study is designed as an exploratory, hypothesis-generating investigation with a focus on identifying biomarkers and predictive signatures associated with POD. Rather than relying solely on a fixed total sample size, the study aims to include a sufficient number of patients with incident POD to enable meaningful exploratory analyses.

Specifically, the target is to observe 100 patients who develop POD. Based on historical incidence rates of POD in older surgical patients, including data from a systematic review of 3533 patients across 19 cohort studies [14], the pooled incidence of POD is estimated at approximately 24% (72/300) overall, with variation depending on the type of surgery (mixed noncardiac 23%, orthopedic 27%, and tumor 19%). Given this expected incidence, it is anticipated that approximately 200 to 300 patients will need to be enrolled to achieve the target number of POD cases. Recruitment will therefore continue until the required number of POD cases is reached.

We acknowledge that even with this sample size, high-dimensional omics analyses remain at risk of overfitting. To address this, feature selection, regularization techniques, and nested cross-validation will be applied to enhance the robustness and reproducibility of the findings. As such, the study is explicitly designed as an initial exploratory investigation, and any identified biomarker signatures or predictive models will require validation in larger, independent cohorts.

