### Blood Sampling and Analysis

In addition, 20 mL of venous whole blood will be collected in ethylenediaminetetraacetic acid, serum, RNA exact, and DNA exact tubes (Sarstedt) at 4 points in time: during premedication, immediately postoperatively, on the second postoperative day, and on the fifth postoperative day. Serum and plasma samples, proteins, DNA, and RNA will be extracted from these whole blood samples. Furthermore, specific cell fractions such as neutrophils, macrophages, and peripheral blood mononuclear cells will be isolated. Proteins will be isolated from these cell samples and, together with plasma, subjected to the proteomic analysis using mass spectrometry to identify potentially significant proteins. Concurrently, an analysis of candidate genes, such as ACHE, BCHE, CHRNA7, chemokines, and cytokines, will be conducted to investigate methylation processes associated with the occurrence of POD. For methylation analysis, DNA samples are subjected to bisulfite conversion, and methylation will be quantified using quantitative polymerase chain reaction with specific primers [17]. The activity of acetylcholinesterase and butyrylcholinesterase will be assessed using ELISA (enzyme-linked immunosorbent assay).

In addition, an in silico analysis of the identified target genes will be performed to identify potential polymorphisms. Polymorphisms that appear potentially relevant will be genotyped in the entire patient cohort using the TaqMan Assay (TaqMan SNP Genotyping Assays; Thermo Fisher) [18,19]. In the final step, the identified genes and proteins will be quantified together with known inflammatory markers (tumor necrosis factor-α, interleukin-6 [IL-6], and interleukin-10) from serum samples using ELISA or the LegendPlex assay (BioLegend) [20]. The blood plasma obtained during cell isolation will also be used for measuring tumor necrosis factor-α and other cytokines (IL-6, interleukin-10, etc) via ELISA. In addition, neuron-specific enolase and S-100 β protein levels will be determined from the remaining blood preoperatively and 48 hours and 5 days postoperatively. The remaining DNA, RNA, and plasma samples will be stored at −20 °C and −80 °C to ensure the possibility of repeat measurements in case of technical errors. The samples will also be preserved for further validation of significant proteins from the proteomic analysis using ELISA and to investigate their genetic basis (polymorphisms and DNA methylation).

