### Integrative Data Analysis and AI Model Development

This section describes the planned integration and analysis of clinical and multiomics data for the exploratory investigation of potential predictors of POD. Data will be analyzed both independently and in combination with a focus on patient groups with and without POD. Prior to analysis, clinical datasets will be preprocessed; for example, variables with more than 30% missingness will be discarded, whereas remaining gaps will be imputed, where applicable, when missing at random, using multiple imputation by chained equations or other suitable methods. Clinical continuous variables will be centered and scaled to *z* scores, and categorical variables will be one-hot encoded. In proteomics, the analysis will involve deriving accurate quantitative protein data from peptide data, particularly by improving the utilization of shared peptides found in multiple proteins.

Univariate analyses, such as *t* tests and ANOVA (with adjustments for multiple comparisons), will be applied to identify candidate features, which may subsequently be subjected to pathway and enrichment analyses to generate mechanistic hypotheses regarding molecular processes potentially involved in POD. Multivariate techniques, including principal component analysis and clustering, will be applied to uncover latent patient phenotypes beyond a priori groupings.

The significant findings from clinical and omics data are fed into a knowledge base for targeted searches, facilitating focused investigations (targeted proteomics). The entire dataset is also analyzed using multivariate methods, including principal component analysis and clustering, to reveal latent patient phenotypes beyond a priori groupings. Supervised prediction of POD will rely on a benchmark suite of algorithms (eg, regularized logistic regression, random forests, support vector machines, and gradient-boosting methods). Model training and hyperparameter tuning will follow a nested cross-validation scheme, supplemented by a temporally separated holdout set when sufficient data are available. Discrimination and calibration will be reported with area under the receiver operating characteristic curve, area under the precision-recall curve, sensitivity, specificity, accuracy, and *F*-score. The final modeling protocol will be chosen on the basis of performance, interpretability, and clinical plausibility and can be iteratively updated as additional data accumulate.

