### Strengths and Limitations

The CONFUSED study has several strengths. First, it employs a prospective observational design with standardized perioperative data collection and systematic delirium assessments using validated instruments (CAM and CAM-ICU). Second, blood samples are collected at multiple perioperative time points, enabling the investigation of dynamic molecular changes associated with the onset and progression of delirium.

Third, the study integrates multiple layers of molecular data, including proteomics, transcriptomics, DNA methylation, and genetic polymorphisms. This multiomics approach provides a comprehensive view of the biological processes involved in the delirium development. Finally, the application of ML methods for data integration and predictive modeling may improve the identification of clinically relevant biomarker signatures.

Several limitations should be considered. First, the study was conducted at a single center, which may limit the generalizability of the findings to other clinical settings or patient populations. Second, although the planned sample size is sufficient for exploratory analyses, validation in independent cohorts will be necessary to confirm the predictive performance of the identified biomarkers and models.

Third, the high dimensionality of multiomics data combined with a relatively moderate sample size may increase the risk of overfitting in predictive modeling. To address this challenge, appropriate statistical methods, cross-validation strategies, and feature selection approaches will be applied. Finally, while peripheral blood samples provide valuable information about systemic biological processes, they may not fully capture neurobiological mechanisms occurring within the central nervous system.

Other challenges should be considered. Privacy and security concerns, the need for extensive and diverse datasets, and the complexity of translating AI findings into clinical practice are notable hurdles [27-29]. While AI can identify associations and patterns, understanding the underlying mechanisms of POD and establishing causality requires further research.

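### The only tests named for the candidate-feature screen carry no covariate, so for the mechanistic aims it can pick up markers of operation type and loses precision on postoperative features

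*Protocol article*

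**What the plan says.** In the protocol article, Integrative Data Analysis and AI Model Development, the screen is introduced with "Univariate analyses, such as" t "tests and ANOVA (with adjustments for multiple comparisons), will be applied to identify candidate features". No covariate, preoperative value or repeated-measures structure is named. Significant findings then go into a knowledge base for targeted proteomics, and candidate features may go on to pathway and enrichment analysis.

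The same article supplies reasons to adjust:

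- Sample Size Considerations gives POD incidence "with variation depending on the type of surgery (mixed noncardiac 23%, orthopedic 27%, and tumor 19"%.
- The Introduction states: "Risk factors for POD include preoperative impaired cognitive and general health status, frailty". Comparison With Prior Work adds age, existing cognitive impairment and type of surgery.
- Blood Sampling and Analysis schedules draws "during premedication, immediately postoperatively, on the second postoperative day, and on the fifth postoperative day", so there is one preoperative and three postoperative samples per patient.
- Strengths and Limitations presents the repeated samples as "enabling the investigation of dynamic molecular changes associated with the onset and progression of delirium".

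**The concern.** Textbox 1 of the article pools hip and knee replacement, femoral neck fracture, spinal disc and visceral surgery. Suppose a protein tracks the type of operation, and the type of operation also tracks POD risk. The protein will then differ between POD and non-POD patients with no link to delirium within any surgery type. A multiplicity correction makes every feature's threshold stricter, but it does not remove this shift, and the shift becomes easier to detect as the study grows.

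The second issue is precision. A two-group comparison of a postoperative level leaves stable between-patient variation in the error term. It also does not look at change, although change is what the article says repeated sampling is for.

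Delirium-associated genes, proteins and epigenetic signatures are a stated secondary objective, and the hits determine where targeted proteomics looks next. Entering clinical variables later in the prediction models does not repair a follow-up list that was already formed without them.

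**Working it through.** The article gives no power calculation or error rate for the screen, so there is no figure of its own to reproduce here. Two quantities were checked.

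**1. False flags from surgery type**

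Inputs from Sample Size Considerations: orthopedic 27%, tumor 19%, and "the pooled incidence of POD is estimated at approximately 24% (72/300) overall", which gives 72 cases and 228 controls at 300 patients. Assumptions: two surgery types in a 1:1 mix, and a feature that differs by D = 1 or 2 within-type SD between them and is unrelated to POD within type.

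- Orthopedic share among cases: 0.27 / (0.27 + 0.19) = 0.587.
- Orthopedic share among controls: 0.73 / (0.73 + 0.81) = 0.474.
- Difference in share: 0.113, so the spurious mean difference is 0.113 × D.
- Pooled SD: √(1 + D²/4) = 1.118 (D = 1) or 1.414 (D = 2). Standardized shift: 0.101 or 0.160.
- Standard error factor: √(1/72 + 1/228) = 0.135. Noncentrality: 0.101/0.135 = 0.75, or 0.160/0.135 = 1.18.

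Rejection rates of the unadjusted test (normal approximation):

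| Threshold | D = 1 | D = 2 |
|---|---|---|
| 5% | 11.6% | 21.9% |
| 0.1% | 0.55% | 1.75% |
| Bonferroni, 1,000 features (0.005%) | 0.05% | 0.20% |

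The target is different: "the target is to observe 100 patients who develop POD". At 24% incidence that needs 100/0.24 = 417 patients. With 417 patients and the same contrast, the 5% row becomes 14% and 28%, and the Bonferroni row 0.07% and 0.36%. In simulation (4,000 runs, 417 patients) the unadjusted test rejected in 13% and 28% of runs. Adding surgery type as a covariate brought this back to about 5%.

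A much steeper contrast changes the picture. With an assumed 40% versus 10%, D = 1 and 300 patients, the rates are 77% at nominal 5% and 8.5% after Bonferroni over 1,000. The article gives no rates of that kind.

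**2. Precision from the preoperative value**

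With pre/post correlation ρ (not given in the article, so assumed), the residual SD falls to √(1 − ρ²), and the equivalent gain in sample size is 1/(1 − ρ²). Power is for a 0.5 SD effect, 72 versus 228, Bonferroni over 1,000 features:

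| ρ | Sample-size factor | Power |
|---|---|---|
| not used | 1.00 | 36% |
| 0.3 | 1.10 | 43% |
| 0.5 | 1.33 | 59% |
| 0.7 | 1.96 | 87% |

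Features measured in the preoperative sample, and genotype, gain nothing.

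**The case against.** **Adjustment is unstated, not excluded.** A reader might infer that the plan rules out covariates. It does not: the two tests are given as examples, and Trial Status refers to a statistical analysis plan that is not shown and may specify more. What stands is that every test the article names is univariate and the only adjustment it names is for multiplicity. If the unseen plan does adjust, the article's sentence should say so.

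**The preoperative sample is used elsewhere.** A reader might infer that it is ignored throughout. The integrative model is to use all four time points, and the preoperative clinical model includes surgical type, age and the Mini-Mental State Examination (MMSE) score. The point is confined to the screen.

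**The bias is modest.** A reader might expect a candidate list dominated by surgery markers. The article's own contrast does not support that once multiplicity is handled. The check also uses the widest pair of rates from an external review and an orthopedic/tumor mix. Textbox 1 has no tumor category, and no POD rates are given for its four groups. Age and cognition cannot be quantified at all, and entry at age 75 or over, a delirium risk score of 5 or more and the exclusion of severe dementia narrow both.

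**Adjustment has a price.** It is tempting to call the precision gain free. POD is not randomized. If the preoperative level itself predicts POD, conditioning on it turns the question into postoperative level given baseline and can remove true signal. Adjusting for MMSE may likewise remove markers of existing vulnerability. This stands, and it is why the adjusted analysis should sit beside the marginal screen and not replace it.

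**The study is exploratory.** This is true, and independent validation is required. For prediction, a marginal screen is legitimate.

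**Conclusion.** The point holds for the mechanistic aims: pathway analysis and the choice of targets for proteomics. The article names only covariate-free tests while itself stating the risk gradients and collecting the variables needed to deal with them.

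The false-flag rate is about 12% to 22% at nominal 5% for features that differ by 1 to 2 SD between surgery types, and well under 1% after Bonferroni over 1,000 features. These rates rest on the 27% versus 19% contrast, an assumed 1:1 mix and 72 versus 228 patients. The forgone precision on postoperative features equals 1.10 to 1.96 times the sample size, resting entirely on an assumed correlation of 0.3 to 0.7.

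This is a worthwhile improvement in method. It does not show that the screen is invalid for prediction.

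**What to change.** Keep the marginal screen for prediction. Beside it, specify one linear model per feature and time point, with false discovery rate control across features:

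- **Postoperative samples:** feature ~ POD + surgery type + age + the same feature's preoperative value.
- **Preoperative features:** their own model, feature ~ POD + surgery type + age.
- **Sensitivity analysis:** add MMSE to each.

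Base the selection for pathway analysis and targeted proteomics on hits that persist after adjustment, and report marginal and adjusted results side by side.

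The cost is wording in the analysis plan and a few degrees of freedom per model. Surgery type, age, MMSE and the preoperative sample are already collected. The downside to state openly is that the baseline-adjusted model answers a conditional question, the postoperative level given baseline. A feature that drops out after adjustment is therefore not thereby shown to be irrelevant to POD risk.

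### Markers chosen by POD status are re-measured and modelled in the same patients, with nested cross-validation stated only for fitting and tuning, so internal AUCs can be optimistic

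*Protocol article*

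**What the plan says.** In the protocol article, the section Integrative Data Analysis and AI Model Development analyses the data "with a focus on patient groups with and without POD". It uses t tests and ANOVA, adjusted for multiple comparisons, to find candidate features. It continues: "The significant findings from clinical and omics data are fed into a knowledge base for targeted searches, facilitating focused investigations (targeted proteomics".

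The section Blood Sampling and Analysis says that, as a last step, "the identified genes and proteins will be quantified together with known inflammatory markers" by ELISA or a multiplex assay on serum samples. Polymorphisms in the identified genes are genotyped across the whole cohort. The first objective in the Introduction makes the differentially expressed genes and proteins the foundation of the models.

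On validation, the article says: "Model training and hyperparameter tuning will follow a nested cross-validation scheme". A temporally separated holdout is added only if the data suffice. Sample Size Considerations lists feature selection, regularization and nested cross-validation together as the protection against overfitting, without placing the first inside the last. No section sets patients aside from marker discovery.

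**The concern.** Nested cross-validation gives an honest AUC only if the held-out patients played no part in choosing the features. Here a panel is picked because it separates POD from no POD, assayed again in the same people, and then modelled. Each outer fold contains patients whose outcomes helped to choose the panel. Unlike a filter in code, an assay panel fixed once cannot be chosen afresh in each training fold.

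Two results are exposed: the internal AUC of any model that uses the selected panel, and its comparison with the preoperative clinical model. The latter has a listed predictor set and is not fed by the biomarker screen, so the comparison can tilt towards omics. Developing predictive models is the primary objective, and the Discussion expects a focused marker panel to emerge for later assays. The internal figure may therefore decide what goes forward.

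A minor related point is the clinical data step: "Prior to analysis, clinical datasets will be preprocessed", including imputation and scaling, with no statement that these are refitted within folds.

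**Working it through.** **The plan's own figures.** The article states no AUC, optimism, selection level or feature count. Its only numbers that bear on this are in Sample Size Considerations: "the target is to observe 100 patients who develop POD", "approximately 200 to 300 patients will need to be enrolled to achieve the target number of POD cases" and "the pooled incidence of POD is estimated at approximately 24% (72/300) overall".

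- 0.24 × 300 = 72 reproduces, and 0.24 × 200 = 48.
- 100 / 0.24 = 417, so 100 cases do not fit 200 to 300 patients. They would need an incidence of 100/300 = 33% to 100/200 = 50%.

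That mismatch is a separate matter. The check below uses both 100/200 and 72/228 (POD/no POD), with similar results.

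**Assumptions not in the documents.** There are 1000 or 5000 independent normal features. Selection is by Bonferroni 5%, Benjamini-Hochberg (BH) 5%, unadjusted p<0.05, or the 20 smallest p values. Signal is either none, or 10 or 30 true features shifted by d = 0.3 or 0.4 SD. Re-measurement reliability is 1, 0.8 or 0.5.

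**Method.** A ridge classifier is assessed by 5-fold outer and 5-fold inner cross-validation, with 20 to 30 replicates per setting. Monte Carlo error of a mean AUC is estimated at about 0.01. If nothing is selected, AUC is set to 0.5.

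- Outside: features selected once on all patients, and only the model cross-validated.
- Inside: selection repeated in each outer training fold.
- New: the all-patient model scored in 1500 new patients.
- Overstatement = outside − new.

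**No true signal (range over both sample splits and both feature counts)**

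| Selection | Outside | Inside | New |
|---|---|---|---|
| Bonferroni or BH 5% | 0.50 to 0.53 | 0.50 | 0.50 |
| Top 20 | 0.81 to 0.89 | 0.49 to 0.51 | 0.50 |
| p<0.05 unadjusted | 0.88 to 0.997 | 0.49 to 0.52 | 0.50 |

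Adjusted selection is nearly unbiased here because it usually selects nothing. Re-measurement in the same patients weakens the leak but does not remove it. At 100/200 with 5000 noise features, top 20 falls from 0.87 (exact) to 0.81 at reliability 0.8 and 0.69 at 0.5. Unadjusted selection falls from 0.995 to 0.98 and 0.84.

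**True signal (100/200, 5000 features)**

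| Selection | True features, d, reliability | Outside | Inside | New | Overstatement |
|---|---|---|---|---|---|
| BH | 10, 0.3, 1 | 0.510 | 0.501 | 0.506 | 0.004 |
| BH | 30, 0.3, 1 | 0.647 | 0.538 | 0.580 | 0.067 |
| BH | 10, 0.4, 1 | 0.666 | 0.557 | 0.613 | 0.053 |
| BH | 30, 0.4, 1 | 0.841 | 0.648 | 0.768 | 0.073 |
| BH | 30, 0.4, 0.8 | 0.761 | 0.581 | 0.686 | 0.075 |
| Top 20 | 10, 0.3, 1 | 0.885 | 0.543 | 0.566 | 0.319 |
| Top 20 | 30, 0.4, 1 | 0.925 | 0.788 | 0.821 | 0.104 |

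A repeat of the simulation gave 0.06 to 0.09 for BH when real signals were selected. Adjusted selection thus overstates by roughly 0 to 0.09, and top 20 by 0.10 to 0.32.

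With BH, in-fold selection fell below the new-patient AUC by up to 0.768 − 0.648 = 0.12. A likely reason is that each training fold has only four fifths of the patients, so fewer features pass the threshold. The corrected estimate is conservative there, not exact.

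**The case against.** The strongest reply is that the article never states the whole chain in one place. Candidate features are said to go on to pathway analysis, significant findings to a knowledge base, and the link to the models comes from an objective in the Introduction. That the screen uses every patient is inferred from the absence of a split; the entire cohort is named only for genotyping. Listing feature selection beside nested cross-validation can be read as selection within the folds, and fold-level detail may sit in the unseen SAP.

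This stands for models built on the untargeted data. It does not rescue the re-measured panel, which is fixed before any fold is formed.

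A reader might also infer that the reported performance will be strongly inflated and that any omics gain is mostly selection bias. The documents do not support that. They carry forward significant findings after multiplicity adjustment, and under such rules the bias was modest. The large figures need top-k or unadjusted selection, which the article neither states nor excludes.

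Some other points for the plan also stand. Markers named in advance (for example ACHE, BCHE, CHRNA7, the known cytokines, neuron-specific enolase and S-100 β) are not chosen by this screen. The models are called exploratory, external validation is required, and the preoperative clinical model is the main bedside tool. These limit the harm but do not correct the AUC reported from this cohort. The conditional holdout helps only if its patients also stay out of discovery, which is not said.

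**Conclusion.** The concern holds in direction; its size depends on a selection rule that the article leaves partly open. With BH or Bonferroni selection, internal AUCs for models using the selected panel can be too high by roughly 0 to 0.09, and the apparent gain over the preoperative clinical model can be too high with them. With top-20 selection, pure noise would appear as 0.81 to 0.89, and with unadjusted p<0.05 higher still. These sizes rest on the assumed feature counts, effect sizes, independence of features and ridge model. The direction rests on the stated re-measurement in study samples and on reading the undivided cohort as the discovery set. Imputation and scaling of the clinical data outside the folds is a minor point and was not quantified.

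**What to change.** In Integrative Data Analysis and AI Model Development, state the following.

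- Every selection step that uses POD status is repeated inside each outer training fold, and the outer fold is used only for scoring. As a minor addition, imputation and scaling are refitted there too.
- For targeted panels chosen from study patients, either the temporal-holdout patients are kept out of marker discovery, or same-patient performance is labelled apparent.
- Validated performance is quoted only from patients not used for discovery: that holdout or the planned independent cohort.

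The cost is wording, more computing and lower reported AUCs, which under in-fold BH selection may be somewhat too low. Labelling needs no patients. Reserving patients shrinks the discovery set. With 135 enrolled by February 2026 and 200 to 300 planned, at most 200 − 135 = 65 to 300 − 135 = 165 later enrollees could be held back. At 24% that is about 0.24 × 65 = 16 to 0.24 × 165 = 40 POD cases. Holding back all of them would leave about 0.24 × 135 = 32 cases for discovery, so a smaller reserve may be preferred. The decision should come before later enrollees enter marker selection, because the option is then lost.
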